### Interventions

In the HVNI arm, patients will receive oxygen therapy through the Vapotherm high-velocity therapy 2.0 via a single-prong nasal cannula (Unicorn). Initial settings are flow rate of 35 L per minute [14], temperature of 37 °C, and fraction of inspired oxygen (FiO_2_) titrated up to 1.0 to achieve target oxygen saturation (SpO_2_). The titration algorithm will be to maintain flow rate at 35 L per minute when tolerated to optimize CO_2_ washout. If intolerance occurs (eg, agitation or discomfort), stepwise reduction in flow by 5 L per minute will be performed to the minimally tolerated level while maintaining target SpO_2_. Adjustments in temperature and FiO_2_ will be up to the attending physician’s discretion to achieve the target SpO_2_ value. Flow rate may be uptitrated as tolerated upon assessment of respiratory rate, work of breathing, and comfort. Study investigators will verify that the single-prong cannula remains securely positioned in the nostril and has not been dislodged due to patient movement. Mouth state (open vs closed) will be recorded at each assessment time point as open-mouthed breathing may reduce the effectiveness of nasopharyngeal dead-space washout. If the cannula is found to be displaced, it will be repositioned immediately, and the event will be documented. Persistent inability to maintain cannula position will be recorded as a protocol deviation.

In the NIPPV arm, patients will receive ventilation through the Respironics V60 respirator (Philips Healthcare) with an oronasal mask of appropriate size. Initial settings are IPAP of 12 to 20 cm H_2_O, EPAP of 5 to 10 cm H_2_O, and FiO_2_ of up to 1.0 to achieve the target SpO_2_. The titration algorithm will be to adjust IPAP to alleviate dyspnea and reduce respiratory rate and PaCO_2_, adjust EPAP for oxygenation and to counter intrinsic positive end-expiratory pressure when indicated, and optimize mask fit to minimize leak.

Cointerventions such as bronchodilators, systemic steroids, antibiotics, diuretics, and other standard-of-care therapies are permitted as clinically indicated and should follow departmental protocols. To reduce confounding, all cointerventions will be documented with time stamps. Initiation of major therapy changes will be avoided within 10 minutes preceding scheduled ABG draws when clinically safe.

### Oxygen Targets and Monitoring

All patients will be put on continuous pulse oximetry. For presumed acute respiratory acidosis without known chronic hypercapnia, SpO_2_ will be maintained above 95%, and for known or suspected chronic hypercapnia with acute decompensation, SpO_2_ will be kept between 88% and 92%. Each patient’s target range will be declared at baseline and maintained throughout the initial 60-minute assessment window unless clinical changes require adjustment. FiO_2_ will be titrated to maintain the declared target. Physiologic monitoring will include vital signs per ED standard, with respiratory rate recorded at baseline, 30 minutes, and 60 minutes.

### Rescue, Failure, and Crossover Criteria

The independent attending physician may change modality or escalate care if deterioration occurs. To standardize decisions, treatment failure is defined by any of the following: persistent or worsening acidosis (pH decrease ≥0.03 from baseline or pH <7.25 with respiratory rate of >30 breaths per minute after 30 minutes of therapy, PaCO_2_ increase ≥5 mm Hg at 30 minutes compared with baseline, and SpO_2_ persistently below target for >5 minutes despite FiO _2_≥0.8 [or the maximal tolerated settings]), severe intolerance to the device (eg, sustained agitation or inability to tolerate the interface) despite comfort measures, and clinical signs of impending respiratory failure (eg, decreasing consciousness, marked fatigue, and hemodynamic deterioration). Intubation criteria follow departmental standards for acute respiratory failure and will be applied consistently in both arms. All crossovers and intubations will be recorded with timing and reason.

### Outcome Measures

The primary outcome is the percentage change in PaCO_2_ from baseline to 60 minutes after initiation of therapy. Baseline is defined as the pretreatment ABG obtained before initiation of the assigned therapy (HVNI or NIPPV). This ensures that the primary outcome reflects the ventilatory effect of the intervention itself. The 30- and 60-minute assessment time points are measured from the time of therapy initiation. The ABG results and other variables (Table 1) to be collected will be documented in real time on paper-based CRFs by trained study investigators.

**Table 1. T1:** Summary of recorded patient variables in a noninferiority randomized controlled trial comparing high-velocity nasal insufflation (HVNI) vs noninvasive positive pressure ventilation (NIPPV) for type 2 respiratory failure in adult emergency department patients at National University Hospital, Singapore.

Variables	Measure
Primary outcome measure	Change in PaCO_2_^a^ at 60 min obtained after initiation of HVNI or NIPPV compared to baseline (before initiation of therapy)
Secondary outcome measures	Change in PaCO_2_ at 30 min compared to baseline Changes in respiratory rate 30 and 60 min after initiation of HVNI or NIPPV Modified Borg Dyspnea Scale at 30 and 60 min Treatment failure Conversion to another modality of oxygenation Requirement for intubation in the emergency department Adverse events due to therapy
Demographics	Age Gender Ethnicity BMI
Comorbidities	Congestive cardiac failure Ischemic heart disease Atrial fibrillation Chronic obstructive pulmonary disease Asthma Obstructive sleep apnea Diabetes mellitus Bronchiectasis Restrictive lung disease Neuromuscular disease Opioid or benzodiazepine use
Vital signs	Temperature Heart rate Respiratory rate Systolic and diastolic blood pressure Mean arterial pressure Glasgow Coma Scale
Investigations	Chest x-ray findings Arterial blood gas results at 0, 30, and 60 min
Clinical course and secondary clinical outcomes	Emergency department diagnosis Hospital inpatient discharge diagnosis Length of intensive care unit stay (if any) Length of hospital stay Inpatient mortality

a PaCO_2_: partial pressure of carbon dioxide.

Percentage change (relative difference) as the primary outcome was selected to account for the wide range of baseline PaCO_2_ values expected in a heterogeneous, all-cause T2RF population. An absolute change in PaCO_2_ may disproportionately favor patients with higher baseline values as they have greater room for absolute reduction. The percentage change normalizes the treatment effect relative to each patient’s starting value, facilitating more equitable comparison across the spectrum of disease severity. To address the potential limitation of relative outcomes, a prespecified sensitivity analysis using absolute change in PaCO_2_ at 60 minutes will be conducted to confirm the robustness of the primary finding.

Secondary outcomes include the following: percentage change in PaCO_2_ from baseline to 30 minutes; change in respiratory rate at 30 and 60 minutes; modified Borg Dyspnea Scale (0-10) at 30 and 60 minutes [24]; proportion of treatment failure (as defined above), conversion to another modality of oxygenation, and need for intubation in the ED; adverse events due to therapy rendered (eg, facial pressure injury, vomiting, or aspiration); length of intensive care unit (ICU) and hospital stay; and inpatient mortality. Inpatient mortality will be assessed at hospital discharge. ICU length of stay (if applicable) and total hospital length of stay will be recorded in days from the date of ED presentation to the date of ICU discharge and hospital discharge, respectively. These data will be abstracted from the electronic health record (EHR) following patient discharge.

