High-velocity nasal insufflation (HVNI) is a specific implementation of high-flow therapy that uses smaller-bore cannulae to deliver higher-velocity flow, generating greater nasopharyngeal pressure at comparable flow rates and enhancing washout of extrathoracic dead space [12]. Early studies suggest that HVNI may be noninferior to NIPPV for composite outcomes such as the need for intubation in mixed populations, with preliminary subgroup findings in patients with T2RF; however, these analyses are limited by design (eg, subgroup or post hoc) and predominance of COPD [13,14]. A single-prong asymmetric-flow nasal cannula design (Unicorn; Vapotherm Inc) has been proposed to facilitate carbon dioxide (CO_2_) egress and improve dead-space clearance at lower total flow rates, which may be advantageous for patients with unilateral nasal patency, facial trauma, or indwelling tubes [15]. Clinical trial data demonstrating ventilation benefits of such single-prong HVNI in T2RF are currently lacking.

While high-flow modalities are generally well tolerated, they are not without risk. Reported adverse effects include nasal dryness or irritation, epistaxis, and rare barotrauma [16,17]. Other considerations include infection control and aerosol generation, which depend on interface fit and clinical context [18,19]. Balanced against the known limitations and intolerance of NIPPV, there is a clear rationale to test whether HVNI can provide comparable ventilatory efficacy in the ED while maintaining better tolerability.

This noninferiority randomized controlled trial is designed to determine whether HVNI delivered via nasal cannula in a single-prong configuration is noninferior to NIPPV for improving ventilation in ED patients with T2RF from any cause. We hypothesize that HVNI will be noninferior to NIPPV with respect to reduction in partial pressure of CO_2_ (PaCO_2_) over an early, clinically relevant time frame, with secondary outcomes including intubation, treatment tolerance, and safety.

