### Statistical Analysis Overview

The primary analysis will follow an intention-to-treat approach, with supportive per-protocol analysis excluding major deviations (eg, early crossovers or missing postbaseline ABG values) and a safety set analyzed as treated. The main end point, percentage change in PaCO_2_ at 60 minutes, will be assessed using analysis of covariance (ANCOVA) adjusting for baseline PaCO_2_ and prespecified covariates (eg, etiology, baseline pH, and age). Noninferiority will be concluded if the upper bound of the 2-sided 95% CI for the HVNI–NIPPV adjusted difference is below the 4.3% margin. A prespecified sensitivity analysis will repeat the primary ANCOVA model using absolute change in PaCO_2_ at 60 minutes as the dependent variable to assess whether the conclusions are robust to the choice of relative vs absolute outcome metric. Secondary endpoints (percentage PaCO_2_ changes at 30 minutes, respiratory rate, and modified Borg Dyspnea Scale) will use similar adjusted models, whereas binary outcomes (treatment failure, intubation, and adverse events) will be compared using chi-square or Fisher exact tests and logistic regression, and length of stay and mortality will be assessed via nonparametric or time-to-event and logistic methods. Missing data handling will focus primarily on the primary outcome (percentage change in PaCO_2_ at 60 minutes). Missing 60-minute ABG results may occur due to early treatment crossover, intubation before the 60-minute time point, patient refusal of repeat ABG, or technical failure of the ABG analyzer. Multiple imputation by chained equations will be performed, with the imputation model including baseline PaCO_2_, baseline pH, treatment arm, age, etiology, respiratory rate, and 30-minute PaCO_2_ (if available). A minimum of 20 imputed datasets will be generated, and results will be pooled using the Rubin rules.

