Using early change in PaCO_2_ as the primary outcome represents both a strength and a limitation. PaCO_2_ directly reflects alveolar ventilation and offers an objective, timely measure of ventilatory response. However, it is a surrogate that may not fully capture longer-term clinical effectiveness, and its relationship to ventilation is nonlinear across baseline values; equivalent absolute changes can imply different physiological effects at different baseline PaCO_2_ levels [30]. Early reductions may overestimate clinical benefit in some patients, particularly those presenting with severe hypercapnia and very high baseline PaCO_2_ levels. Accordingly, interpretation of the primary end point will be integrated with prespecified secondary outcomes and sensitivity analyses. If noninferiority is established with acceptable safety and tolerance, subsequent clinical trials focused on patient-centered and longer-term outcomes, including cost-effectiveness and broader implementation, would be warranted.

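### Treatment tolerance is announced as a secondary outcome but appears in neither outcome list, and the Borg dyspnea score has no stated baseline for its adjusted model

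*Protocol article*

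**What the plan says.** **Tolerance.** The Introduction gives the rationale as "comparable ventilatory efficacy in the ED while maintaining better tolerability" and describes the trial "with secondary outcomes including intubation, treatment tolerance, and safety". The Discussion makes later trials conditional: "If noninferiority is established with acceptable safety and tolerance". The secondary outcomes in Table 1 and in the text of Outcome Measures are PaCO2 change at 30 minutes, respiratory rate, Borg, treatment failure, conversion to another modality, intubation in the ED, therapy-related adverse events, length of stay and inpatient mortality. None is called tolerance. In Rescue, Failure, and Crossover Criteria, severe intolerance of the device is one of several conditions that define treatment failure. The same section has the timing and reason of every crossover recorded.

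**Dyspnea.** Table 1 has "Modified Borg Dyspnea Scale at 30 and 60 min" and the text has "modified Borg Dyspnea Scale (0-10) at 30 and 60 minutes". Neither mentions a pre-therapy rating. Respiratory rate is different: Oxygen Targets and Monitoring plans it "with respiratory rate recorded at baseline, 30 minutes, and 60 minutes". Table 1 has arterial blood gases at 0, 30 and 60 minutes.

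**Analysis.** Statistical Analysis Overview specifies the primary ANCOVA as "adjusting for baseline PaCO_2_ and prespecified covariates (eg, etiology, baseline pH, and age". Of the secondary endpoints it says "respiratory rate, and modified Borg Dyspnea Scale) will use similar adjusted models". All secondary endpoints are exploratory.

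**The concern.** Two parts of the article that describe the same set of outcomes disagree. Tolerance matters here because it is a main reason for offering an alternative to mask ventilation and a stated condition for going further. Left inside a composite, it is mixed with acidosis, rising PaCO2, hypoxemia and impending respiratory failure. The trial's rationale expects HVNI to do better on tolerance, while the margin accepts that it may do somewhat worse on PaCO2. These are opposite directions within one proportion, so similar failure rates could hide a real difference in each component.

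For Borg, the model that its analysis is to resemble draws on the starting value of its own endpoint. If no pre-therapy Borg is taken, the corresponding covariate does not exist, change in dyspnea cannot be reported, and a chance difference in starting dyspnea cannot be adjusted for directly. A missed baseline cannot be recovered later.

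**Working it through.** **1. Where each endpoint has a baseline**

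| Endpoint | Baseline stated in the text shown | Follow-up | Planned model |
|---|---|---|---|
| PaCO2 | yes (0 min, Table 1) | 30, 60 min | ANCOVA with baseline PaCO2 and other covariates |
| Respiratory rate | yes (Oxygen Targets and Monitoring) | 30, 60 min | similar adjusted model |
| Borg | none | 30, 60 min | similar adjusted model |

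**2. Where tolerance is captured**

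- Severe intolerance: a component of treatment failure.
- Conversion to another modality: its own outcome, for any cause. It is not named among the binary outcomes in Statistical Analysis Overview.
- Crossover reason: recorded, but not listed as an outcome.
- Adverse events: interface injury and similar harms, not whether the device was tolerated.

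If each failure is assigned to one first trigger, the arm difference in the composite is the sum of the component differences: D(failure) = D(intolerance) + D(gas exchange) + D(other). A negative first term and a positive second term can cancel. Only separate reporting shows them.

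**3. The number of patients per arm**

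The documents give no figure for Borg or tolerance, so the only plan figure used is 42 per arm (Sample Size). It reproduces: n = 2 × (1.96 + 0.84)² × 6.65² / 4.3², rounded up to 38 per arm. With the 10% allowance, 38 × 1.10 = 41.8, so 42 per arm and 84 in total.

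**4. What a baseline Borg would add**

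The correlation r between pre-therapy and follow-up Borg is not in the documents. It is assumed, with range 0.3 to 0.7. Against a model with no other covariates:

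- residual variance factor = 1 − r²
- equivalent increase in patients = 1/(1 − r²) − 1
- detectable difference, in SD units, at 80% power and two-sided 5% = (1.96 + 0.84) × √(2/42 × (1 − r²))

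| r | Variance factor | Reduction | Equivalent extra patients | Detectable difference |
|---|---|---|---|---|
| no baseline | 1.00 | – | – | 0.61 SD |
| 0.3 | 0.91 | 9% | 10% | 0.58 SD |
| 0.5 | 0.75 | 25% | 33% | 0.53 SD |
| 0.7 | 0.51 | 49% | 96% | 0.44 SD |

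These gains are upper limits for each r. The planned model may already include baseline PaCO2, pH, age and etiology, which would be expected to explain part of the same variation. The table also assumes Borg ratings from all 42 patients per arm.

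**5. Timing**

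As of July 2026, 19 of 84 patients were enrolled (Results). That leaves 84 − 19 = 65, or 77%, for whom a baseline could still be taken.

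**The case against.** Much of the case on the other side stands.

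- **Tolerance data exist.** A reader might infer that the trial cannot report tolerability by arm. The documents do not support that: severe intolerance is a defined failure criterion, conversion and therapy-related harms are separate outcomes, and crossover reasons are recorded. What is missing is a separately named outcome, not the information.
- **The margin does not rest on tolerability alone.** Sample Size bases it on clinician judgment and literature on PaCO2 response. The Discussion also cites simpler operation and use where a mask is contraindicated.
- **The Borg model can be fitted.** Statistical Analysis Overview does not say that baseline Borg is a covariate. Follow-up Borg regressed on arm, baseline PaCO2, pH, age and etiology is a valid analysis under randomization. A chance imbalance in starting dyspnea is already reflected in the confidence interval.
- **A baseline Borg may be planned.** Figure 1 is not shown and the article condenses a fuller protocol. The absence is established only for the text and Table 1.
- **The gain is uncertain.** It rests on an assumed correlation and shrinks with the other covariates in the model and with any missing baselines.
- **The endpoints are exploratory,** and the Discussion leaves patient-centered outcomes to later trials.

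These points limit the size of the problem. They do not explain why an outcome announced in the Introduction is absent from both lists, or why Borg alone among the continuous endpoints given these models has no stated baseline.

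**Conclusion.** The point holds as an inconsistency in the outcome definitions and an avoidable loss of precision. It does not threaten the primary analysis. Treatment tolerance is promised and not listed; as listed, its effect is visible only through outcomes that mix causes. Borg, as scheduled in the text and Table 1, cannot be adjusted for its own baseline or reported as change. If Figure 1 does list a baseline Borg, this second part reduces to stating it in the text and naming it as the covariate.

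A reader might conclude that the dyspnea comparison would be biased. It would not be: randomization protects it, and only precision is lost. The size is a reduction in residual variance of at most 9% to 49% for an assumed correlation of 0.3 to 0.7, or a detectable difference of 0.58 to 0.44 SD instead of 0.61 SD, before allowing for the other covariates.

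**What to change.** 1. List device intolerance as its own secondary outcome, reported by arm, in both Table 1 and the text of Outcome Measures. Build it from the severe-intolerance failure criterion and the crossover reasons already recorded. The Introduction and the outcome lists then agree. Where the failure criterion met can be identified from existing records, this needs no new data and can cover all 84 patients.
2. Record Borg once before therapy starts, if this is not already done, and name it as the covariate in the Borg model.

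**Cost.** One CRF line and a short amendment. The 19 patients enrolled by July 2026 may lack a baseline Borg, as may some later patients whose mental capacity is impaired (Ethical Considerations). The Borg analysis would then need to impute the baseline or be restricted to later patients, and the choice should be stated in advance. No extra comfort scale is needed, and reporting of missingness for each outcome is already planned.

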### Blinding

Due to the nature of the interventions, participants, treating clinicians, and bedside nursing staff cannot be blinded to group allocation. ABG is analyzed at the bedside using i-STAT Alinity (Abbott Laboratories). Device allocation will not be recorded on ABG stickers or forms to minimize detection bias. The data analyst performing the primary and secondary outcome analyses will also be blinded to treatment allocation and will receive deidentified datasets with treatment arms coded (eg, group A and group B) without revealing the intervention assignment. Data entry staff who are not involved in clinical care will be trained to abstract outcomes using standardized case report forms (CRFs). Nevertheless, the primary outcome evaluated is objective and should not be confounded by lack of blinding [23].

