### Quality Assurance and Monitoring

Study investigators will undergo training on device application, titration protocols, mask fitting and leak management, and CRF completion. An independent data monitoring and safety team within the institution will conduct periodic reviews to assess protocol adherence, data completeness, and safety. Any serious adverse events related to the study interventions will be reported to the National Healthcare Group Domain Specific Review Board per institutional requirements. Quarterly adherence checks will include verification of device settings, oxygen targets, ABG timing windows, and documentation of cointerventions.

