This single-center trial design supports consistent implementation but may limit generalizability to settings with different resources or experience with HVNI. Blinding of patients, health care providers, and research staff is not feasible and may influence subjective measures and escalation decisions. These risks are mitigated by an objective primary end point, standardized timing of ABG sampling, predefined escalation criteria, and complementary intention-to-treat and per-protocol analyses. In addition, while PaCO_2_ levels at 30 and 60 minutes provide a clinically relevant and objective indicator of early ventilatory response, PaCO_2_ is a surrogate outcome of short-term response and does not fully capture longer-term ventilation success or failure. Physiologically, reduction in PaCO_2_ levels may be related to increased minute ventilation brought about by dyspnea rather than true clinical improvement. Patients with T2RF from COPD and neuromuscular diseases often follow a progressive disease trajectory and require extended ventilatory support to prevent delayed clinical deterioration, and taking PaCO_2_ measurements in the early treatment window may fail to reflect longer-term clinical effectiveness of the intervention [29]. Finally, the use of percentage change in PaCO_2_ as the primary outcome, while it accounts for baseline severity differences, may introduce variability in treatment effect estimation across patients with heterogeneous baseline values. The relationship between PaCO_2_ and alveolar ventilation is nonlinear such that equivalent percentage changes may represent different physiological magnitudes at different baseline levels.

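### The adverse-event outcome compared between arms counts only events attributed to therapy, in an open-label trial with no blinded causality assessment stated

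*Protocol article*

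**What the plan says.** The condition appears in both places where the outcome is defined. Table 1, under Outcome Measures, lists "Adverse events due to therapy". The text of the same section gives "adverse events due to therapy rendered", with facial pressure injury, vomiting and aspiration as examples. Neither place lists a count of adverse events regardless of cause.

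Statistical Analysis Overview treats adverse events as a binary outcome, compared between arms by chi-square or Fisher exact test and logistic regression, and mentions a safety set analysed as treated. Secondary endpoints are declared exploratory, without multiplicity adjustment.

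On masking, the Blinding section states that "participants, treating clinicians, and bedside nursing staff cannot be blinded to group allocation". The Discussion extends this to research staff: "Blinding of patients, health care providers, and research staff is not feasible and may influence subjective measures and escalation decisions". Only the data analyst is described as blinded. Data entry staff outside clinical care abstract outcomes, but they are not said to be blinded or to judge cause.

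Quality Assurance and Monitoring adds that "Any serious adverse events related to the study interventions will be reported to the National Healthcare Group Domain Specific Review Board per institutional requirements".

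**The concern.** An event enters this outcome only after someone has decided that the therapy caused it. That decision is a judgement, and nothing in the article places it with a person unaware of the device. The ease of the judgement also differs by type of event. Facial pressure injury under a mask hardly needs one. Vomiting and aspiration, the other two examples given, occur in acutely ill patients with hypercapnia whatever the interface, so the same event may be put down to the device in one arm and to the disease in the other.

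The Discussion accepts that lack of blinding "may influence subjective measures and escalation decisions". The mitigations it then lists are the objective primary endpoint, standard blood gas timing, predefined escalation criteria, and the two analysis populations. None of them bears on attribution of adverse events. Coding the arms for the analyst does not help either, because the analyst receives events that have already been filtered.

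At stake is the tolerability and safety message. The Discussion makes follow-on trials depend on noninferiority together with acceptable safety and tolerance, and it says that the hoped-for advantages of HVNI will be weighed alongside safety outcomes.

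**Working it through.** **No stated figure to reproduce.** The article gives no adverse-event rate and no attribution rate. The one figure used from it is the arm size of 42 (Sample Size). That figure is sound: 2 × (1.960 + 0.842)² × 6.65² / 4.3² = 37.5, so 38 per arm, and a 10% allowance gives 42 (38 × 1.1 = 41.8) or 43 (38 / 0.9 = 42.2). The present point does not change it.

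**Passages side by side.**

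| Secondary outcome | Attribution to therapy required? |
|---|---|
| Adverse events (Outcome Measures, Table 1 and text) | Yes, in both places |
| Treatment failure (Rescue, Failure, and Crossover Criteria) | No |
| Conversion to another modality | No |
| Intubation in the ED | No |
| Inpatient mortality | No |

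**Illustration (all rates assumed).** Let the true risk p be the same in both arms, and let a_N and a_H be the shares of events called due to therapy under NIPPV and HVNI.

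- Counted risks: p × a_N and p × a_H.
- False difference: p × (a_N − a_H).
- False risk ratio: a_H / a_N, whatever the value of p.

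The last column is the exact probability of Fisher P≤0.05 with 42 per arm, summed over both binomial distributions.

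| True risk | a_N / a_H | Counted NIPPV vs HVNI | False difference | P≤0.05 |
|---|---|---|---|---|
| 20% | 90% / 90% | 18% vs 18% | 0 | 2.9% |
| 20% | 90% / 60% | 18% vs 12% | 6 points | 7.5% |
| 20% | 90% / 45% | 18% vs 9% | 9 points | 15.0% |
| 30% | 90% / 90% | 27% vs 27% | 0 | 3.0% |
| 30% | 90% / 60% | 27% vs 18% | 9 points | 11.7% |
| 30% | 90% / 45% | 27% vs 13.5% | 13.5 points | 26.2% |
| 40% | 90% / 90% | 36% vs 36% | 0 | 3.1% |
| 40% | 90% / 60% | 36% vs 24% | 12 points | 16.4% |
| 40% | 90% / 45% | 36% vs 18% | 18 points | 38.0% |

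The false risk ratio is 0.60 / 0.90 = 0.67 in the middle scenario and 0.45 / 0.90 = 0.50 in the more unequal one. Swapping the arms gives the same probabilities with the opposite sign. If every event counts regardless of cause (a_N = a_H = 1), the expected difference is 0 and P≤0.05 occurs in 2.9% to 3.4% of trials.

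**The case against.** **Serious harms are counted elsewhere.** A reader might infer that attribution governs the safety comparison as a whole, so that harm from inadequate support on HVNI could disappear as disease. The documents do not support that. Falling consciousness, marked fatigue and haemodynamic deterioration are signs that define treatment failure, with no causal test. Failure, conversion, ED intubation and inpatient mortality are separate outcomes, and every crossover and intubation is recorded with its time and reason. This objection stands and limits the point to the adverse-event outcome.

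**The serious-event sentence.** It is tempting to read "Any serious adverse events related to the study interventions will be reported" as meaning that deaths or arrests judged unrelated are lost. The sentence concerns notification to the ethics board. It does not define the analysed outcome, and the preceding sentence has an independent team review safety with no relatedness limit. Deaths are counted as inpatient mortality in any case.

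**Who judges.** The article does not name the person who decides attribution. That this person knows the device is an inference from the unblinded roles. What the text does establish is that no blinded assessor is stated.

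**Condensation.** Causality procedures and collection windows are commonly left to the full protocol, and their absence here is no finding. The attribution condition, however, is not absent: it is written into the outcome in two places. A later analysis plan cannot recover events that were never logged because they failed it.

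**Size and noise.** The rates above are assumed, and one trial may show little: 7 vs 4 counted events of 42 gives Fisher P=0.52. All-cause counting also brings background disease events, which can mask a real device difference, and an as-treated set does not have the full protection of randomisation. These remarks are fair. They argue for keeping relatedness as a descriptive column and for adding a comparison by randomised arm. They do not argue for testing only the attributed events.

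**Conclusion.** The point holds in a narrow form. The adverse-event outcome, as defined and tested, depends on a causal judgement that no stated procedure protects from knowledge of the device, so the comparison is open to differential attribution. The direction is unknown: easier attribution to the mask would flatter HVNI, and closer scrutiny of the novel interface would do the reverse. On the assumed rates the false difference runs from 6 to 18 points, and false significance from 7.5% to 16.4% of trials with moderately unequal attribution and from 15% to 38% with more unequal attribution. These figures rest on equal true risk of 20% to 40%, 42 patients per arm, and attribution of 90% against 60% or 45%; none of these rates comes from the documents.

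The consequence is limited. One exploratory secondary comparison is affected, and the primary noninferiority test is not. This is an inexpensive improvement worth making, not a flaw that threatens the trial's main result.

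**What to change.** In Outcome Measures (text and Table 1), redefine the outcome as the occurrence of adverse events regardless of attributed cause:

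- Use one checklist in both arms. It should cover the effects named for either device: facial pressure injury, vomiting and aspiration from Outcome Measures, and nasal discomfort, mucosal dryness and epistaxis from the Discussion. Add serious events.
- Count events within one fixed window from the start of therapy, for example to ED departure or to 24 hours, the same for both arms.
- Compare the outcome by randomised arm, alongside the planned as-treated safety set.
- Report relatedness as a descriptive classification only, ideally judged without knowledge of the arm.

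Ethics-board reporting stays as the institution requires.

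The cost is a change to the outcome wording and the case report form, more events to log, and some background noise from the underlying illness. No new staff or procedures are needed. The article reports 19 of 84 enrolled as of July 2026, so a change made at that point would cover the remaining 65 (77%) prospectively. For those already enrolled, the checklist would have to be completed from records where possible, with any gap reported.
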